## Methods

### Study design

The INTEGRATE study is a clustered stepped-wedge randomized controlled trial with a waiting list control group. A flowchart of the study and a timeline is shown in Figures 1 and 2, respectively. All participants are offered the intervention (PPA CMR) during the study period. The intervention is implemented over four time periods, in randomly ordered subgroups. The intervention group starts with PPA CMR at onset of the study, the control group starts with PPA CMR one year later. The one year waiting list period is necessary to measure natural changes in lifestyle and to estimate the number of patients with newly detected CMD without exposure to PPA CMR.

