### Endpoints and measurements

The endpoints of the INTEGRATE study are shown in Table 2. An overview of all measurements is shown in Figure 2.

**Table 2 T2:** Primary and secondary endpoints

**Primary endpoints**	**Secondary endpoints**
1. The number of newly detected patients with a CMD in one year follow-up	1. Difference in primary outcome 5 after implementation of different response-enhancing strategies
2. Change in individual risk factors (smoking, physical inactivity, obesity, unhealthy diet, blood pressure and cholesterol levels) for CMD between baseline and one year follow-up	2. Change in willingness to change lifestyle between baseline and one year follow-up
3. The expected number of newly detected patients with CMD and mortality after 5, 10,20 years and lifetime	3. Change in health status between baseline and one year follow up
4. Costs-effectiveness of PPA CMR	
5. Non-participation and compliance in different stages of PPA CMR	

For our secondary endpoints we will use the information provided for our primary endpoints.

1. *Newly detected patients with CMD at baseline and one year follow-up*

The number of newly detected patients with pre-existing CMD will be established after the second consultation and after one year follow-up, based on ICPC-1-coded diagnoses (see Table 1) in the EMRs.

2. *Change in individual risk factors for CMD between baseline and one year follow-up*

For patients with an increased risk for CMD, risk and lifestyle profiles will be established at the start of PPA CMR and after twelve months of follow-up. Risk profiles consist of the completed risk profile including the additional measurements done by the GP or with the self-management toolbox. The questions of the online risk estimation and lifestyle assessment are repeated after six months as well (see Figure 2).

For patients with a low risk for CMD we will establish risk and lifestyle profiles at the start of PPA CMR and after twelve months of follow-up. These risk profiles do not contain the additional measurements.

3. *Expected newly detected patients with CMD and mortality after 5, 10, 20 years and lifetime*

We will use the RIVM-Chronic Disease Model (RIVM-CDM) [28,29] to extrapolate the number of possible prevented CMD due to PPA CMR with a time horizon of 5, 10 and 20 years. The calculations are based on changes in risk profile during one year of treatment.

4. *Costs-effectiveness of PPA CMR*

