#### Waiting list control group

From the waiting list control group we establish risk profiles, lifestyle assessment, health status, work status and absence from work at baseline and again at the start of PPA CMR one year later. At the start of PPA CMR newly detected patients with CMD will be established, based on ICPC-1-coded diagnoses in the EMRs. Patients who develop a new CMD - documented through an ICPC-1-coded diagnoses in the EMR - will not be eligible for participation in PPA CMR, but will receive questionnaires for follow-up. When the waiting list control group starts with the intervention phase, the patients follow the identical route as the intervention group (see Figure 2).

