#### Effectiveness of PPA CMR

We will use multivariable multilevel regression analyses to study the effects of PPA CMR on change in individual risk factors and lifestyle and on the incidence of CMD after one year follow-up. Therefore, we compare the intervention group with the waiting list control group. In addition we will evaluate the influence of different response enhancing strategies on the effectiveness of PPA CMR. We will use linear or logistic regression for continuous or dichotomous data, respectively. Multilevel analysis is needed to correct for clustering of patients within practices.

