#### Cost-effectiveness of PPA CMR

We will perform an economic evaluation to relate net incremental costs and effects of PPA CMR compared to the waiting list control group. Estimated costs are based on the healthcare and non-healthcare costs. After one year of follow-up, cost-effectiveness of PPA CMR will be established. To evaluate cost-effectiveness in the long term, modeling is required. We will use the RIVM-Chronic Disease Model (RIVM-CDM) to perform this long-term economic evaluation. The RIVM-CDM is a Markov-type, dynamic population-based model [28,29] and is able to relate changes in prevalence of risk factors to changes in future incidence of CMD. The model also contains data on costs of cardiovascular events and associated losses in quality of life. This model has extensively been used for the evaluation of cost-effectiveness of prevention programs targeted at lifestyle improvement [34,36-38].

The cost-effectiveness will be calculated per level of change in individual risk factors. Incremental cost-effectiveness ratios (ICER) are derived from calculating the net costs of PPA CMR compared to the waiting list control group, divided by its effect. In addition, we will calculate the incremental cost-utility ratios (ICUR). Therefore, the incremental costs of PPA CMR compared to the waiting list control group will be divided by the effects in quality adjusted life years (QALY’s) gained. Utility values as incorporated in the RIVM-CDM will be used for future cardiovascular events. Probabilistic sensitivity analysis are performed for all calculations.

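### As written, the model input for primary endpoint 3 is a change within treated patients, not the difference from the waiting list that a projected programme effect requires

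*Protocol article*

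**What the plan says.** Table 2 of the protocol article lists expected future CMD and mortality as primary endpoint 3. Under Endpoints and measurements, item 3, the RIVM-CDM is used "to extrapolate the number of possible prevented CMD due to PPA CMR with a time horizon of 5, 10 and 20 years". The next sentence gives the input: "The calculations are based on changes in risk profile during one year of treatment".

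Other sections describe the control contrast:

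- Study design: "The one year waiting list period is necessary to measure natural changes in lifestyle", and also to estimate newly detected CMD without the programme.
- Waiting list control group: risk profiles and lifestyle are recorded "at baseline and again at the start of PPA CMR one year later".
- Effectiveness of PPA CMR: for the one-year analysis of risk factors and CMD incidence, "Therefore, we compare the intervention group with the waiting list control group".
- Cost-effectiveness of PPA CMR: the evaluation is to "relate net incremental costs and effects of PPA CMR compared to the waiting list control group", and "We will use the RIVM-Chronic Disease Model (RIVM-CDM) to perform this long-term economic evaluation".

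The section Control group says that waiting-list patients complete an online questionnaire at baseline and receive neither a risk score nor specific lifestyle advice during the waiting year.

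**The concern.** The output of endpoint 3 is causal: disease prevented because of the programme. The stated input is change during a year of treatment. Waiting-list patients have no such year before their own programme starts, so the sentence naturally describes a before-after change in treated patients.

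A before-after change mixes three things: the programme effect, change that would have happened anyway, and regression to the mean. The last is a real possibility here. Body mass index and waist circumference enter the score that decides who goes on to the practice measurements, so patients above the threshold are partly selected on values that tend to move back on repeat measurement.

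The existing safeguard does not address this. The Modeling item under Choices in study design names one source of long-term overestimation, fading of the effect after the first year, and relies on probabilistic sensitivity analysis. That analysis varies inputs around their estimates. It cannot show that an input contains natural change.

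At stake is a primary endpoint intended to inform a decision on national implementation, in a trial that has randomised controls available.

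**Working it through.** **1. The plan's own figures.** The article gives no numerical result for the projection. The nearest figures are in Sample size calculation: smoking falls from 25% to 20% with treatment, the number of smokers on the waiting list is stable, alpha is 0.05 two-sided, power is 0.80, allocation is 1:4, and 721 intervention patients are needed. The continuity-corrected formula for two proportions (20% against 25%, four controls per intervention patient) gives 721, an exact match; without the correction it gives 696. So the planned 5-point effect is a contrast with controls who stay at 25%. This confirms the reading of the inputs but does not bear on endpoint 3 directly.

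**2. The sections side by side.**

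| Section | Quantity | Comparator stated |
|---|---|---|
| Endpoints and measurements, item 3 | Change during a year of treatment, fed to the RIVM-CDM | None |
| Effectiveness of PPA CMR | Risk factors and CMD incidence at one year | Waiting list |
| Cost-effectiveness of PPA CMR | Costs and effects, long term through the RIVM-CDM | Waiting list |
| Choices in study design, Modeling | Effect of PPA CMR on risk profiles | Implied only |

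The between-group statements concern the one-year analysis and endpoint 4. None is made for endpoint 3.

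**3. Size of the discrepancy, using smoking.** Let G be the fall in the intervention group and D the fall in the waiting list. The net effect is G − D, and the ratio of a gross to a net input is G / (G − D). G = 5 points comes from the plan. D is not given beyond being stable, so every non-zero value below is an assumption.

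- D = 0 (the plan's assumption): 5 / 5 = 1.00, no bias.
- D = 0.5: 5 / 4.5 = 1.11, overstated by 11%.
- D = 1: 5 / 4 = 1.25, overstated by 25%.
- D = 2: 5 / 3 = 1.67, overstated by 67%.
- D = −1 (controls worsen by 1 point): 5 / 6 = 0.83, understated by 17%.

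These are ratios of model inputs. They carry over to smoking-related cases prevented only roughly, to the extent that the model responds in proportion to the change in prevalence.

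**4. Which risk factors have a control change.** Endpoint 2 includes blood pressure and cholesterol. For intervention patients these are taken at the practice after a score above the threshold (The risk estimation and lifestyle assessment; Completing the CMD risk profile). For controls, the text describes only an online questionnaire at baseline. The section Waiting list control group does say that risk profiles are established at baseline, but the article uses that term both with the additional measurements (increased-risk patients) and without them (low-risk patients). Figure 2, which might settle the matter, is not shown. On the visible text, a control change is clearly available for the questionnaire items and uncertain for blood pressure and cholesterol.

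**The case against.** The strongest reply is that the endpoints section leaves out comparators by habit. Endpoint 2 is also worded as change between baseline and one year, yet the Abstract and Effectiveness of PPA CMR make clear that it is compared between groups. Endpoint 3 draws on the same changes, its output is defined causally, and the Modeling item speaks of extrapolating the programme's effect. On that view the coherent reading is one model and one set of net effects, and a condensed article may leave the exact input to an analysis plan.

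Much of this stands. A reader might infer that the sponsor will definitely use uncontrolled changes, or that endpoints 3 and 4 will definitely run on different inputs. The documents do not support either inference: no sentence excludes subtracting the control change, and several sections point towards it.

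It does not remove the point. For endpoint 2 another section supplies the comparator; for endpoint 3 none does. The article does not leave the input to a later document: it states one, and the input stated does not match the quantity claimed. For blood pressure and cholesterol, an uncontrolled change may also be the one most readily at hand.

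The objection on size and direction also stands. The non-zero drifts are assumptions for one risk factor. The Background describes a growing number of people with an unhealthy lifestyle, so worsening among controls is as conceivable as improvement.

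**Conclusion.** The point holds as a defect in what the text fixes. Followed literally, the stated input makes a primary endpoint an uncontrolled before-after projection, in conflict with its causal output and with the contrast used for the economic evaluation on the same model. If a net input is intended, the sentence misdescribes the plan and still needs correcting.

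Neither size nor direction is established. For smoking the bias is zero under the plan's stable-control assumption. The 11%, 25% and 67% are illustrations for assumed control falls of 0.5, 1 and 2 points; a 1-point control rise would give a 17% understatement. It would be wrong to conclude that the projected benefit is overstated by any of these amounts. The stable-control assumption covers smoking only, and the trial includes a waiting year precisely because natural change cannot be taken as known.

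The correction should be made, with medium confidence that it changes what an analyst would do.

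**What to change.** In Endpoints and measurements, item 3, replace the input sentence with wording such as: The model input is the difference between the intervention and waiting-list groups in one-year change in each risk factor, estimated from the multilevel models, with its uncertainty carried into the probabilistic sensitivity analysis. State that the same input serves endpoints 3 and 4.

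Where a risk factor has no control baseline (on the visible text, possibly blood pressure and cholesterol), show its contribution to the projection separately and label it uncontrolled. If the projection is run for patients above the risk threshold, compare them with controls above the same threshold; the control questionnaire includes the risk estimation questions, so this can be done without telling controls their score.

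Cost: one sentence for factors with control data, since the planned effectiveness analysis already yields those estimates. Separating any factor without a control baseline takes more work and could change the headline projection. The projected benefit may be smaller and its uncertainty wider. The change does not deal with selective response after randomisation, which the article already acknowledges.

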#### Response-enhancing strategies

During this study we will develop and evaluate different response-enhancing strategies in subgroups of the waiting list group. The response enhancing strategies are adjusted according to the results of non-response analyses performed early in the study (see next paragraph, endpoint 5). Possible strategies include reminders by telephone, translated questionnaires for non-Dutch speaking patients, information gatherings at the general practice and verbal reminders by the GP.

Another strategy is using a toolbox to complete the final risk profile at home. It offers the option to bypass one or both of the GP consultations. The toolbox contains a blood pressure device and a laboratory test form. Patients are asked to measure their blood pressure, visit the laboratory and to complete the results online. In case of a high blood pressure and/or elevated serum cholesterol or glucose levels, patients are advised to consult their GP. Patients without elevated biomedical risk factors receive an online tailored lifestyle advice and will therefore bypass both GP consultations. Like the other response-enhancing strategies, the toolbox option will be implemented during the intervention period of the waiting list control group.

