Participation rates in the different phases of PPA CMR are measured by establishing the number of participants and the number of eligible patients in each stage (after the first invitation, after completion of the online risk estimation, after completing the risk profile and during the treatment phase). Data about the numbers of participants in each phase can be derived from the website for online respondents. The number of practice visits and compliance with treatment is established at six and twelve month with data from EMRs and self-reported compliance. We will collect information on determinants of response and non-response through the use of three different sources. First, we will send questionnaires to a random sample of patients who did not respond to the invitation of their GP for participating in PPA CMR (non-response group 1). This non-response questionnaire contains items on health risk behavior, assumptions about CMD and screening, reasons for not participating and attitudes towards response-enhancing strategies (see Table 3). In addition, we will send a comparable online non-response questionnaire to patients who scored above the threshold on the online risk estimation, but did not consult their GP (non-response group 2). Second, we will extract anonymized data from EMRs, including information on health care utilization of both participants and non-participants. Finally, all data will be linked with data from Statistics Netherlands to obtain information about socio-economic status (SES) and ethnic background.

**Table 3 T3:** Overview of measurements among non-responders

**Non-response questionnaire**	**T=0**	**T=12**
Risk estimation (paper)	*	
Online risk estimation and lifestyle profile	o	o
Attitude towards screening and treatment of CMD	•	
Reasons for non-participation	•	
Attitude towards response-enhancing strategies	•	
Newly detected CMD (EMR)		•
Health care utilization (EMR)		•

* = Non-responders group 1 (no response to invitation PPA CMR, no online risk estimation).

o = Non-responders group 2 (score above threshold on risk estimation, but not no GP consultation).

• = All non-responders (group 1 + 2).

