Information on determinants of non-participation and successful completion of PPA CMR is used to study the differences in characteristics of responders and non-responders. We will also study differences in characteristics of participating practices (e.g. urban/rural locations, solo/group practices, organization of lifestyle interventions) to find practice-related factors that are associated with participation and compliance rates. The analyses of determinants for participation shall be performed in the first groups starting with the intervention. Depending on the findings, response-enhancing strategies are developed and implemented in the waiting list control groups that subsequently enter the study. Data collection for subgroups receiving a response enhancing intervention is done in the same way as described above.

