### Non-response analyses

The results of the non-response analyses of the INTEGRATE study will provide more information about the characteristics and motives of non-participants in PPA CMR. This knowledge is relevant and essential for the development and evaluation of participation enhancing strategies. The INTEGRATE study has a unique design where the results of the non-response analyses, performed at an early time point during the study, can be used as input for developing interventions to increase the participation rate later in the study. Effective participation enhancing strategies are useful when optimizing implementation of future prevention programs in primary care.

In comparable studies, including the pilot implementation of PC [14,15] the response rates were low, ranging from 3% to 75% [14,15,18]. Since this has been taken into account in the sample size calculation, sufficient power is expected even with low response rates. To enhance participation rates we plan to use several strategies, based on advise and results of previous studies [14] and on non-response analyses during the study. The accompanying information letter will emphasize safety in handling privacy sensitive data, especially digital data. Furthermore, the information letter will contain a short recap of the purpose of the letter and the advice to ask a family member for help with translation if considered necessary. The letter will present the recap in different languages. Reminder letters with a paper version of the risk estimation will be sent to all non-responders after two weeks. Furthermore, we evaluate a subgroup that is offered the possibility to bypass one of the GP consultations by ordering a toolbox. The toolbox is a tool that stimulates self-management; patients are able to take more responsibility for their own health. Furthermore, obtaining the additional measurements through a toolbox is easier to incorporate into ones busy life and this might enhance participation rates. A higher participation rate increases the cost-effectiveness of the entire program.

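### The rule for non-response group 2 (above threshold, no GP consultation) also captures toolbox users with normal results, whom the stage count treats as participants

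*Protocol article*

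**What the plan says.** Five statements in the protocol article bear on this point.

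- *Group 2.* Under endpoint 5 in Endpoints and measurements, one of the two non-response questionnaires goes to "patients who scored above the threshold on the online risk estimation, but did not consult their GP (non-response group 2"). The Table 3 footnote repeats the criterion: "Non-responders group 2 (score above threshold on risk estimation, but not no GP consultation"). Its double negative is evidently a slip, and read with the body text it means that no GP consultation took place. Neither place makes an exception for the toolbox.
- *Toolbox.* Response-enhancing strategies says of the toolbox: "It offers the option to bypass one or both of the GP consultations". It separates two outcomes. "In case of a high blood pressure and/or elevated serum cholesterol or glucose levels, patients are advised to consult their GP". By contrast: "Patients without elevated biomedical risk factors receive an online tailored lifestyle advice and will therefore bypass both GP consultations". Users enter their results online.
- *Carry-over.* At the end of endpoint 5: "Data collection for subgroups receiving a response enhancing intervention is done in the same way as described above".
- *Counting.* Endpoint 5 obtains participation rates from the participants and eligible patients at each stage, and completion of the risk profile is one of the stages. Endpoint 2 accepts measurements taken by the GP or with the toolbox as part of that profile.
- *Use.* Secondary endpoint 1 in Table 2 is "Difference in primary outcome 5 after implementation of different response-enhancing strategies".

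The Non-response analyses part of the Discussion describes the toolbox differently. There a subgroup is "offered the possibility to bypass one of the GP consultations by ordering a toolbox".

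**The concern.** The group 2 rule treats a missing GP consultation as evidence that an above-threshold patient dropped out between the risk estimation and the completed profile. That works where the practice visit is the only way to complete the profile. The toolbox adds a second way, and for patients with normal results the absence of a consultation is then the intended end of the route.

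The rule therefore fails in the toolbox subgroup, and among the strategies the article names, only the toolbox can replace consultations. Two things are at stake. Patients who finished the screening would be labelled non-responders and asked for their reasons for not participating, so their answers would be mixed with those of genuine non-responders in that subgroup. And endpoint 5, on which secondary endpoint 1 rests, contains two ways of classifying the same patient, with no statement of which prevails when they disagree.

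**Working it through.** The plan gives no figure for this point. The sample size of 721 concerns smoking prevalence and is not touched. The check is mainly a comparison of rules, made on the text and tables; Figures 1 and 2 were not examined.

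**Step 1: classify each type of above-threshold patient in the toolbox subgroup**

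| Patient | Completed-profile stage count | Group 2 rule |
|---|---|---|
| Measured at the practice | participant | not in group 2 |
| Toolbox, elevated value, then consults GP | participant | not in group 2 |
| Toolbox, elevated value, does not consult | participant | group 2 |
| Toolbox, normal values, no consultation | participant | **group 2** |
| Neither route completed, no consultation | non-participant | group 2 |

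The fourth row is the conflict that arises by design. The third row also differs, but that patient did not follow the advice to consult, so a non-response label has some meaning there.

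**Step 2: does the rule reach the toolbox subgroup?** Yes. The carry-over sentence keeps the data collection unchanged in strategy subgroups, which brings the group 2 rule with it. It brings the stage counts with it as well.

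**Step 3: does it reach the determinants analysis?** No. Endpoint 5 places that analysis in the first groups to start the intervention. The toolbox is introduced later, when the waiting list groups enter their intervention period.

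**Step 4: what would happen if consultation were the criterion for secondary endpoint 1?** The article does not say that it is. Let c0 and c1 be the true completion rates without and with the toolbox, u the share of completers who use it, and e the share of those users who have an elevated value and then consult the GP. Then:

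- completers placed in group 2 = c1 × u × (1 − e)
- apparent gain = c1 − c1 × u × (1 − e) − c0

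All four inputs are assumptions, because the article gives none of them. With c0 = 0.60 and c1 = 0.70 (true gain 10 points):

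- u = 0.10, e = 0.75: 0.70 × 0.10 × 0.25 = 0.0175; apparent gain 0.6825 − 0.60 = +8.25 points
- u = 0.25, e = 0.50: 0.70 × 0.25 × 0.50 = 0.0875; apparent gain 0.6125 − 0.60 = +1.25 points
- u = 0.50, e = 0.25: 0.70 × 0.50 × 0.75 = 0.2625; apparent gain 0.4375 − 0.60 = −16.25 points

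If completion is counted by the completed risk profile, the gain is 0.70 − 0.60 = +10 points in every case.

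**Step 5: one consultation or both?** If the toolbox could replace only one consultation, as the Discussion has it, every toolbox completer would still have a consultation and the group 2 rule would classify them correctly. If it can replace both, as Response-enhancing strategies has it, the rule fails. The two descriptions therefore have different consequences for classification.

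**The case against.** The strongest reply is that the article does not define participation by GP consultation at all. Endpoint 5 is counted by stage, the completed profile may come from the toolbox, and the results are entered online, so a toolbox user with normal values is already counted as a participant. Group 2 appears only in the sentence on who is sent a questionnaire and in the table of measurements among non-responders. Nothing makes it the numerator of endpoint 5 or of secondary endpoint 1.

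Most of this stands, and it rules out several stronger readings that a reader might be tempted to make:

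- *That the toolbox will be made to look ineffective.* This needs group 2 status or consultation to be used for comparing strategies, and the article states no such use.
- *That all successful toolbox users become non-responders.* Only users without elevated values are meant to skip both visits.
- *That the profile of non-responders is contaminated.* The stated determinants analysis precedes any toolbox use.
- *That practice visits define compliance.* The article lists visits and treatment compliance as two separate items.

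The reply does not remove the mismatch itself. The group 2 rule has no exception, it is carried into the toolbox subgroup, and followed as written it labels completers as non-responders and sends them the questionnaire.

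**Conclusion.** The point holds as a definitional inconsistency under endpoint 5. Above-threshold toolbox users with normal results are participants by one stated rule and non-responders by another. The certain consequence is a wrong label and a misdirected questionnaire in the toolbox subgroup.

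An effect on secondary endpoint 1 is conditional, and its size is unknown. The range of +8.25 to −16.25 points against a true +10 rests entirely on assumed rates, including the assumption that every user counted in e does consult the GP. It shows only that the choice of criterion could matter; it does not estimate an error in this trial. No figure in the article changes. The correction is worth making because it removes an ambiguity beneath a named secondary endpoint.

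**What to change.** 1. Define non-response group 2 as patients above the threshold whose risk profile was completed by neither route, that is, neither by measurements at the practice nor by toolbox results entered online.
2. Change the Table 3 footnote to match, and remove its double negative.
3. State that secondary endpoint 1 compares strategies on the completed-risk-profile count by either route.
4. Reconcile Response-enhancing strategies with the Non-response analyses part of the Discussion on whether one or both GP consultations can be bypassed. The definition in item 1 works under either description, so it need not wait for this.

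The cost is protocol wording. No new data are needed, because toolbox results are already entered online, and no clinical rule changes. The wording should be in place before non-response questionnaires go out in the toolbox subgroup.
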